## Discussion

Given the prevalence and burden of transgenerational transmission of mental disorders in COPMI, it is imperative that effective evidence-based prevention interventions be identified and disseminated as a routine part of care for patients with mental illness who are parents and in care of their children. The vulnerable COPMI group struggles with lack of parents’ awareness of mental health issues and the parents are often not aware of the child’s perspective, i.e., the child’s experience of the situation. Issues of stigma can prevent parents from having relevant conversations. For children, it is important understand their parents’ behavior in relation to their mental disorder, while parents need to understand the impact of mental illness on their child’s behavior. Parents and children welcome having information relayed to them by a mental health professional. In the long term, we expect that the ChildTalks+ intervention will reduce emotional problems in COPMI and prevent (further) mental health problems from developing.

The aim of this study will be to introduce and pilot test the preventive ChildTalks+ intervention for children whose parents suffer from a mental disorder. The results should demonstrate the efficacy of the ChildTalks+ methodology, including its sustainability over time, and thereby contribute new knowledge regarding the risk and protective factors acting on COPMI. The results should also objectively describe feasibility of this prevention program that is based on working with children through their parents. Given our specialization on patients with eating disorders, we will address the effects and feasibility of the ChildTalks+ intervention especially with respect to children whose parents have eating disorders.

### Strengths and limitations

One of the strengths of this study is that the program will be based on full adherence to the ChildTalks+ methodology, including training of therapists by authors of the program. We will assess the efficacy of the program in a trial with nearly 70 families where a parent has a mental illness and the family includes children aged 6–18. The study design encourages participation by the entire family, that is, including the partners of persons with mental illness and all children in the family. Potential positive results from the study would support a broader use of the ChildTalks+ methodology in preventive mental health services not only in the Czech Republic but also in other countries. An additional strength is the involvement of mental health professionals as ChildTalks+ therapists. For therapists who work with patients with eating disorders, accessibility and feasibility of the intervention will be documented through additional qualitative data, which should provide information regarding the awareness of risk and protective factors for the disorder. Finally, to avoid high attrition rates, parents and children will be fully informed about requirements related to the study-related prior to enrolment. Therapists will assist parents and children with completing the questionnaires.

A limitation of this study is that parents may find it difficult to talk about their mental health problems because of fears of stigma. Fear of admitting the true extent of their problems may lead to reluctance regarding either their own or their children’s participation in the study. Another limitation is that many parents with mental health problems who are experiencing symptoms of illness have not been diagnosed by a relevant professional and therefore cannot be identified. Finally, there is a limitation related to the age of the children: based on the decision of the Ethics Committee, children younger than 12 or 15 will not be able to complete the questionnaires needed to evaluate the study.

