### Procedure

Therapists will be recruited by a therapist coordinator in collaboration with the project coordinator. Once trained, ChildTalks+ therapists will begin working with families. They will first give the potential candidates information about the ChildTalks+ intervention and about participation in the study. This research study is an essential part of project Implementation and Evaluation of ChildTalks+ in the Czech Republic. If potential candidates express interest, they will be asked if they agree that their other family members be contacted, because our aim is to involve entire families. Participation will, however, be also possible for pairs consisting of just one parent with a mental health disorder and one child aged 6–18. For children aged under 18, parental consent is required for their participation in the study. Participants will receive a timeline regarding the survey measures and delivery of the ChildTalks+ intervention. They will receive reminders of upcoming meetings.

Families will pay nothing for their participation in the project and receive no financial reward. Trained therapists will be financially rewarded for their work with families: the remuneration will cover a total of 10 h of work with each family. This includes direct work with the family using the ChildTalks+ methodology and administration of questionnaires (handing them out, providing instructions for completion, collection of completed questionnaires, and their delivery to coordinators of the implementation team).

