### Allocation into groups

Using a quasi-experimental design, each family will be assigned to a condition (intervention or control group) based on a paired matching. Allocation to a group will be based on the number of identified risk factors in the family [3]. These include mental disorder/comorbidities of the respondent, frequency of hospitalizations, diagnosis of a mental disorder of the other parent, eventually the child or children, absence of another caregiver, ignorance of the respondent’s diagnosis within the family, and low household income. Common demographic data (gender, age, highest educational attainment, the number of adults and children in the household) are also collected from respondents.

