### Assessments

The data will be collected using a variety of questionnaires (described under measures). The questionnaires are completed by parents of children aged 6–18 and children aged 12 and older. Two questionnaires on the list, namely *The Strengths and Difficulties Questionnaire (SDQ)* and *The Youth Mental Health Literacy Scale (YMHL)*, will be completed by children over the age of 15. For children under 12 years of age, the Ethics Committee of the General University Hospital (Prague, Czech Republic) allowed qualitative data to be collected through interviews with the therapist. Participating parents and children will explore areas which are being assessed at the baseline, post-test (T1), and at the follow-ups (T2, T3). All assessments will be conducted using appropriate scales individually with each subject.

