#### Control group (*N* = 33)

Two months after the baseline assessment (T0), post-test assessment (T1) should be performed at the same time as the T1 assessment of the intervention group. Parents and children have a follow-up assessment 6 months from T1 (T2) and 12 months from T1 (T3). After the T3 follow-up assessment, families will receive the ChildTalks+ intervention.

In the qualitative part of the research, we also explore the use of the ChildTalks+ intervention by professionals who treat patients diagnosed with eating disorders. We will gather these qualitative data using semi-structured interviews to explore the feasibility of ChildTalks+ intervention for patients with eating disorders and their offspring, and to describe the therapists’ experiences during the collaboration, including perceived obstacles and positives. The results should also inform us about what parents and children found helpful about the ChildTalks+ intervention. The qualitative data will be assessed by a thematic analysis [65].

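### The therapists who deliver ChildTalks+ also handle, and help complete, the self-report outcome forms; this is liable to cause differential reporting between arms and is cheap to change

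*Protocol article*

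**What the plan says.** Under Procedure, the protocol article sets out what the payment of 10 hours per family covers: "direct work with the family using the ChildTalks+ methodology and administration of questionnaires (handing them out, providing instructions for completion, collection of completed questionnaires", followed by delivery of the forms to the coordinators. Delivery of the intervention and handling of the outcome forms are thus one paid task for each family.

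Strengths and limitations goes a step further: "Therapists will assist parents and children with completing the questionnaires". The sentence closes the strengths paragraph, directly after the statement on avoiding high attrition. The limitations paragraph does not mention it.

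Under Assessments, the quantitative outcomes are self-reports: "The questionnaires are completed by parents of children aged 6–18 and children aged 12 and older", with SDQ and YMHL restricted to children over 15. The same section states: "All assessments will be conducted using appropriate scales individually with each subject". It names no independent administrator and no sealed or direct return.

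The control condition is a delayed intervention: "After the T3 follow-up assessment, families will receive the ChildTalks+ intervention". Allocation is not randomised: "each family will be assigned to a condition (intervention or control group) based on a paired matching".

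**The concern.** Several of the questionnaires ask about what the sessions work on: parent–child communication, sense of competence as a parent, and the child's quality of life and difficulties. At T0 neither arm has had sessions. From T1 on, an intervention family may answer with help from a therapist who has worked with it on those subjects, while a control family has had no sessions. A difference in how families report that arises after T0 enters the between-arm difference in T0–T1 change, which is the immediate effect that Statistical methods tests. The T0–T2 and T0–T3 contrasts are exposed in the same way.

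No treatment-concealed version of these outcomes is available, so some bias of open self-report has to be accepted. Help from the delivering therapist is a further and avoidable source. Once the data are in, the planned analysis cannot separate a change in reporting from a change in the family.

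**Working it through.** **Inputs.** From Sample size and power calculation: difference in change 2.5, SD 4.90, two-sided 5%, power 0.8, paired t-test, 33 pairs. From Statistical methods: contrasts T0–T1, T0–T2 and T0–T3, with Holm adjustment. The differential reporting shift b is not in the document; it is assumed and shown over a range from zero.

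**Step 1: the plan's own figure.** Take 4.90 as the SD of the within-pair difference in change.
- Standard error = 4.90/√33 = 0.853.
- Noncentrality = 2.5/0.853 = 2.93, with 32 degrees of freedom and critical value 2.037.
- Power from the noncentral t = 0.811. With 32 pairs it is 0.798, so 33 is the smallest number that reaches 0.80.

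The stated sample size reproduces and is not in question.

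**Step 2: which part of the influence matters.** Write the observed difference in change as the true effect + (reporting shift in the intervention arm − reporting shift in the control arm). Therapist influence that is equal in both arms drops out, as does influence that is the same at T0 and T1 within an arm. Only the remainder, b, distorts the contrast.

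**Step 3: what a given b would do.** Set the true effect to 0 and the noncentrality to b/0.853. The rejection probability is P(|T| > critical value), where T is noncentral t with 32 degrees of freedom.

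| Assumed b (points) | b / 2.5 | b / 4.90 | Noncentrality | Two-sided rejection at 5% |
|---|---|---|---|---|
| 0 | 0% | 0 | 0 | 5.0% |
| 0.25 | 10% | 0.05 | 0.29 | 5.9% |
| 0.5 | 20% | 0.10 | 0.59 | 8.8% |
| 1.0 | 40% | 0.20 | 1.17 | 20.6% |
| 1.25 | 50% | 0.26 | 1.47 | 29.6% |

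**Step 4: allowance for Holm.** The article does not say which comparisons form the Holm family. If it is the three time points, the strictest step is 0.05/3 = 0.0167, with critical value 2.526. The rejection probability is then 1.7% at b = 0, 10.2% at b = 1.0 and 16.0% at b = 1.25. The rates are lower, but the relative inflation is not removed.

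**Step 5: limits of the arithmetic.** The 2.5 and 4.90 are not tied to a named scale, so a point has no concrete meaning beyond its share of the planned effect. The planned analysis is an adjusted mixed model, for which the paired t-test stands in here. The table would apply to a differential shift from any source. It shows how sensitive the test is and does not estimate the bias in this trial.

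**The case against.** **Direction.** A reader might infer that the arrangement does bias the result, and in favour of the intervention. The document does not establish that. The sessions ask parents to look at the disorder from the child's side and aim to detect children's problems early, so sensitised parents could report more concerns on PEDS or SDQ. Strengths and limitations mentions parents' fear of admitting how serious their problems are; trust built over four sessions could lower that fear and raise reported problems. Social desirability and therapist expectation make benefit the more plausible direction, but not a certain one. This objection stands.

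**Common influence.** Therapists recruit the families, and the text restricts neither handling of forms nor assistance to one arm. Much of the influence may therefore cancel. This also stands, and it limits the concern to the differential part. Payment covers hours per family and does not depend on results, so it adds no differential pressure of its own.

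**What the text leaves open.** A reader might infer that therapists read the answers. Procedure says that they collect and deliver the forms, not that they read them. Nor is it stated outright that each family's own therapist helps with its forms, although one payment per family for both tasks makes that the fair reading. What assisting involves is unspecified and might amount to little more than the instructions already named. Not every measure mirrors the session content: ChEDE-Q covers the child's eating habits.

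**Purpose.** The assistance is offered to limit attrition, which is a legitimate aim with 33 matched pairs, where each lost family can break a pair. This bears on how the change is made, but it does not require help with the answers themselves.

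**Article format.** A condensed article may leave working detail to a fuller document. The point here, however, is a procedure that the article does state and presents favourably.

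**Conclusion.** The concern holds as a risk of differential reporting, not as a demonstrated bias. Three stated facts carry it: the delivering therapists handle the self-report forms, they assist with completion, and only intervention families have had sessions before T1 to T3. The non-randomised, open allocation leaves little else in the design to guard against such a difference.

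The size cannot be derived from the document. On assumed shifts of 0 to 1.25 points, the false-positive rate runs from 5% to about 30% before Holm adjustment. The upper figures should not be read as expected values: at 0.25 points the rate is about 6%. These results assume a paired t-test, 4.90 as the SD of the within-pair difference, and no true effect.

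This is an inexpensive improvement to the procedure. It does not invalidate the design and leaves the sample size unchanged.

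**What to change.** In Procedure and Assessments, for both arms alike:
- Parents and children aged 12 and over complete the questionnaires themselves, keeping the existing age restriction for SDQ and YMHL.
- Forms go back in a sealed envelope or through an online form, directly to the coordinators, who already receive them.
- Therapists hand over the packet and give reminders only. Questions about content go to the coordinators.
- Assistance that cannot be avoided is logged by family, time point and type. Leaving out assisted forms is only a secondary sensitivity analysis, because it selects on something that happens after baseline and breaks pairs.
- In Strengths and limitations, any remaining assistance is listed as a limitation.

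The cost is envelopes or an online form and a few sentences, with no extra staff and no change to the 33 pairs. The downside is some more incomplete items and possibly slightly more attrition, which the retained reminders would partly offset. The bias inherent in open self-report remains.

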### Implication for practice

If implemented in clinical practice, the ChildTalks+ program could be a significant preventive intervention aimed at helping the COPMI. Treatment centers should expand their focus to the entire family, not care for adults in isolation from care for their offspring. Parents struggling with a mental disorder usually do not communicate with their children about their condition and related difficulties. Breaking this silence may improve the parent–child interaction and children may be able to better understand their own as well as their parents’ situation. This may increase the competence of both parents and children, leading to a better quality of life regardless of the severity of parent’s mental disorder.

## Data Availability

Data from projects using this study protocol should be made available to researchers through approved data repositories in accordance with the relevant legislation. The results of this study will be made available to the scientific community through peer-reviewed publications in scientific journals. It is intended that results of this study would be published internationally, presented at conferences, and disseminated through international research groups. Policymakers, public health and social services, and stakeholders will be informed via conferences, websites, newsletters, and personal contacts.

## Abbreviations

COPMI: Children of Parents with Mental Illness
IG: Intervention group
CG: Control group
